#### Viral pneumonia co-infections

Pneumococcal viral co-infection will be defined as any clinical or radiological pneumonia case where both *S. pneumoniae* and RSV or influenza are detected in nasopharyngeal samples. *S. pneumoniae* will be identified by quantitative real-time polymerase chain reaction (PCR) targeting the *lytA* gene (qPCR) [37] and microarray as per testing algorithm [29]. RSV or influenza will be identified by RT-PCR [27]. In addition, for radiologically-confirmed pneumonia cases, pneumococcal viral co-infection will include cases with a positive pneumococcal urinary antigen test and RSV or influenza detected on nasopharyngeal sampling [27].

### Study design

The surveillance programme includes both retrospective (Jan 2015 - Feb 2019) and prospective (March 2019–March 2022) data collection. The study has a number of different components, including prospective pneumonia hospital-based surveillance with a nested case-control study, retrospective pneumonia chart review, data collection regarding other clinically relevant interventions and trends in cardiovascular and renal disease admissions as “control” conditions, and enrolment of controls without evidence of respiratory disease for validation of the urine antigen test [4].

#### Prospective adult pneumonia hospital-based surveillance

##### Recruitment procedures

Prospective adult pneumonia hospital-based surveillance started on 1 March 2019. Participants are adults 18 years and older who are admitted with pneumonia to one of the four participating district hospitals and enrolled in the surveillance system. Hospital staff actively identify and screen all new adult respiratory admissions daily (from admission and other wards) to assess suitability for the study. Details regarding all patients screened, their eligibility and whether they were enrolled or not, as well as reasons for exclusion are captured on a screening/ enrolment log. Study staff review all admissions on a weekly basis to ensure that no eligible patients were missed. Any missed patients will be enrolled at time of identification.

If patients meet the clinical pneumonia case definition and provide written consent to be included in the study, clinical information is collected using an adapted case report form with details regarding presentation (e.g. oxygen saturation on admission), clinical management (e.g. provision and duration of supplementary oxygen) and risk factors for carriage and disease. If patients are unable to give consent – e.g., because of mechanical ventilation, severe illness, or mental incapacity – permission is obtained for enrolment from the next of kin to prevent severe cases from been missed.

Recorded risk factors include previous admissions for pneumonia and other conditions, level of education, recent migration to Ulaanbaatar, household size, number of children in the household, PCV vaccination status of children in the household, dwelling type, history of working in a mine, tobacco smoking, alcohol use, type of heating (coal, briquettes, electric or central) and type of stove in the household, history of tuberculosis, self-reported and documented comorbidities and pregnancy. Details regarding underlying medical conditions, antibiotic use and severity markers, e.g. blood pressure, respiratory rate, and level of consciousness according to the AVPU (“alert, verbal, pain, unresponsive”) scale and Glasgow Coma Scale [34, 35] are collected during medical record review. Prospectively enrolled participants will have digital CXRs, nasopharyngeal swabs and urine collected.

##### Number of subjects

Based on a review of admission rates in previous years we anticipate enrolment of approximately 1000–1500 adults with pneumonia per year in the prospective surveillance system in the four districts. All adults meeting the pneumonia surveillance case definitions will be invited to participate in the study.

##### Eligibility, inclusion and exclusion criteria

Any adult 18 years of age or older admitted to one of the four participating district hospitals and meeting one of the surveillance case definitions for pneumonia will be eligible for inclusion. Exclusion criteria include not residing in one of the four districts for the last 3 months and readmission for pneumonia within 14 days of a previous admission for pneumonia.

##### Informed consent

Only adults who consent will be enrolled. If the nurse or doctor is unable to obtain consent from a patient who is severely ill, ventilated, or otherwise incapacitated, the nurse or doctor will contact the patient’s next of kin to obtain permission to enrol the participant in the study. The next of kin will be provided with the same information as for a participant and be asked to sign the consent form on behalf of the participant.

#### Nested case-control study

This substudy will only include adults residing in households with children eligible to receive PCV13. Vaccine eligibility will be based on the relevant district vaccine introduction timelines. We will confirm household level vaccination data, obtained by verbal report, using clinic or electronic immunisation records if available. Children eligible to receive PCV13, who are identified as unvaccinated, will be referred to their local health centre for catch-up according to local guidelines.

When we identify an adult, who is hospitalised for pneumonia and who has children of vaccine eligible age living in the household, we will seek to enrol the adult and their household in the case-control study. We then conduct three separate case-control analyses (defined below) with respect to having any child in the house who received one or more doses of PCV13 compared with households having all PCV13-unvaccinated children.

The case-control comparison will be done for three endpoint-based subgroups.
Among adults hospitalised with pneumonia and with a CXR consistent with CAP based on clinical assessment at time of hospitalisation, VT pneumococcal pneumonia (case) compared with NVT pneumococcal pneumonia (control) based on serotype-specific urine antigen assays.Among adults hospitalised with pneumonia and with a CXR obtained, those with findings meeting adapted World Health Organization (WHO) paediatric radiological criteria (case) compared with those who have any other radiologic finding (control). This analysis is based on the assumption that pneumococcal pneumonia is more likely to have WHO endpoint consolidation CXR findings than non-pneumococcal pneumonia.Among adults hospitalised with pneumonia and with pulse oximetry performed, those with hypoxia (case) compared with those without hypoxia (control). This analysis is based on the assumption that pneumococcal pneumonia is more likely to be hypoxic than non-pneumococcal pneumonia.

These analyses will be controlled for relevant confounders, such as age and housing type.

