## Background

Adult community-acquired pneumonia (CAP) is an important cause of morbidity and mortality, especially in high-risk groups, both in high- and low-income countries. The burden of pneumococcal pneumonia among adults is not well characterised. Historical estimates were generally based on blood culture results only and therefore underestimated true disease burden [1], or included sputum which may reflect carriage and therefore overestimated burden [2]. Two luminex platform-based multiplex serotype-specific urinary antigen detection (SSUAD) assays have been developed and validated for identification of key *S. pneumoniae* serotypes in urine samples from adults with radiologically-confirmed CAP, which may assist in defining the burden of non-bacteraemic pneumonia [3, 4]. A meta-analysis that included studies utilising additional diagnostics such as the BinaxNOW® *Streptococcus pneumoniae* urine antigen test, attributed 27% of adult CAP to the pneumococcus [1]. This analysis, however, mainly included studies from high-income countries.

Nasopharyngeal pneumococcal carriage is a precursor to pneumococcal disease [5]. Pneumococcal conjugate vaccines (PCVs) protect against colonisation acquisition or density with vaccine-type (VT) and potentially some cross-reactive serotypes, while overall pneumococcal carriage prevalence is only slightly decreased (or unchanged) due to serotype replacement [6]. Nevertheless, reductions in transmission of VT serotypes have resulted in large indirect effects in high-income settings [7] because VTs tend to be more likely to cause disease than replacement serotypes. Indirect or “herd” effects of vaccines refer to the indirect protection of the non-vaccinated population with a reduction in disease or carriage within this group [8].

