To evaluate the association between childhood PCV13 introduction and the trends in incidence of (a) clinical pneumonia or (b) hypoxic pneumonia only (see case definition) in adults 18 years and older in four districts of Ulaanbaatar over a 7 year period (Jan 2015 – Mar 2022).To evaluate the association between childhood PCV13 vaccination (during the early [2019–2020] and late [2021–2022] PCV13 introduction period) and the trends in adult pneumonia (see case definition) in four districts of Ulaanbaatar using the following endpoints: (a) all radiologically confirmed pneumonia, (b) definite pneumococcal pneumonia and (c) VT-pneumonia with a chest radiograph (CXR) consistent with CAP based on clinical assessment at time of hospitalisation.To evaluate the association between childhood PCV13 introduction (during the early and late PCV13 introduction period) and the trends in the detection and density of pneumococci in the nasopharynx of adults admitted with pneumonia.To assess changes in the detection of pneumococcal serotypes (VT and non-vaccine type [NVT]) associated with adult pneumonia in an era of ongoing childhood PCV vaccination.Among adults hospitalised for pneumonia, who have children of vaccine eligible age living in the household, to compare adult cases and controls with respect to having a child in the house who received one or more doses of PCV13 compared with households having all PCV13-unvaccinated children. The case-control comparison will be done for three subgroups: VT (case) compared with NVT pneumococcal pneumonia (control); end-point radiologically-confirmed pneumonia (case) compared with other radiologic findings (control); hypoxic (case) compared with non-hypoxic (control) pneumonia.To evaluate the association between PCV13 introduction in children on the trends in incidence and severity of adult pneumonia associated with viral pathogens (RSV or influenza) in four districts of Ulaanbaatar, during the early and late PCV13 introduction period, for the following endpoints: incidence of severe clinical pneumonia, clinical pneumonia, and radiologically confirmed pneumonia associated with RSV or influenza.

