##### Urine processing

Urine samples from adult cases enrolled prospectively in the adult surveillance programme, will be tested at the NCCD bacteriology laboratory in Mongolia using a rapid pneumococcal urinary antigen test (BinaxNOW®, Alere North America, Orlando, Florida). The BinaxNOW® *Streptococcus pneumoniae* test is an immunochromatographic membrane assay test used to detect pneumococcal soluble antigen in human urine. It detects the pneumococcal C-polysaccharide which is found in the cell wall and is common to all serotypes. BinaxNOW® urine testing conducted at the NCCD bacteriology laboratory will be conducted by two designated trained laboratory technicians according to study standard operating procedures to ensure consistency of results.

Additional urine will be frozen in ultra-low temperature (− 70 °C) freezers before being shipped to the Pfizer Laboratories, Pearl River, USA for pneumococcal testing using multiplex SSUAD assays that assesses the 13 serotypes in PCV13 (UAD1) [4] and the additional 11 serotypes in 23-valent pneumococcal polysaccharide vaccine (PPSV23) (UAD2) [3]. Positivity cut-off limits for the SSUAD assay will be established based on antigen concentrations read off a standard curve for each serotype using the 400 urine specimens collected from control subjects as described above. While UAD cut-points have only rarely been reset based on evaluation of local healthy control subjects, this step ensures test validity and high specificity.

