**Fig. 1 Fig1:**
[figure not shown]
Schematic diagram of study design and timelines

The outcome variable for this analysis will be monthly district-level counts of severe clinical pneumonia. The IRR will be estimated using a mixed effects Poisson loglinear regression model (or a negative binomial model if there is over-dispersion) fitted to monthly counts, with log-transformed population denominators included as an offset. The model will include a fixed effect for PCV13 (indicator variable for PCV13 introduction which will depend on the district as PCV13 introduction was staggered), a fixed effect for time (time since study commencement in months) to account for temporal trends, and a random effect for district. The PCV13 term will be exponentiated to obtain the incidence rate ratio for the vaccine effect. This model assumes that there is uniform vaccine impact across the districts. Sensitivity analyses will explore whether the vaccine impact differs across districts and will include seasonality and employ changes in vaccine coverage as opposed to fixed PCV13 effects. A subgroup analysis will explore rate changes in different age groups (18–25, 26–45, 46–65 and > 65 years). We will also do a sensitivity analysis with a 1 year “lag period” for indirect PCV effect (as we don’t expect the indirect effect to be instantaneous).

For the secondary pneumonia endpoints, no pre-PCV13 radiological and urine data are available. Consequently, we will explore trends over time in the post-PCV13 introduction period, incorporating district and time since PCV13 introduction.

We will conduct a nested case-control analysis (“test-negative design” [46]) to measure the indirect PCV13 vaccine effectiveness among adults living with children eligible to be vaccinated with PCV13. The model will account for district and time since vaccine introduction. We will compare the odds of receiving PCV13 among household children between cases and controls, defined as: 1) adults with vaccine type (cases) versus non-vaccine type pneumonia (controls), 2) among adults who had a CXR, WHO defined radiological confirmed pneumonia (cases) versus no radiological pneumonia (controls) and 3) among adults who had pulse oximetry, hypoxic (cases) versus non-hypoxic (controls) pneumonia.

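### The only serotype-specific case-control contrast is an indirect-cohort comparison, not a test-negative one, so its odds ratio gives indirect vaccine effectiveness only if household PCV13 leaves adult NVT pneumonia unchanged; a second, pneumococcal-negative control group should be added

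*Protocol article*

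**What the plan says.** Three places in the protocol article define the contrast. The list of secondary objectives and the section Nested case-control study both fix NVT pneumococcal pneumonia as the control condition; the latter reads "VT pneumococcal pneumonia (case) compared with NVT pneumococcal pneumonia (control) based on serotype-specific urine antigen assays". The nested case-control paragraph under Statistical analysis plan gives it as "1) adults with vaccine type (cases) versus non-vaccine type pneumonia (controls", without the word pneumococcal.

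The exposure is "having any child in the house who received one or more doses of PCV13 compared with households having all PCV13-unvaccinated children". The stated purpose is "to measure the indirect PCV13 vaccine effectiveness among adults living with children eligible to be vaccinated with PCV13", and the same sentence labels the design test-negative. The model accounts for district and time since vaccine introduction.

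For the radiological and hypoxia contrasts, Nested case-control study states the assumption that makes each one informative about pneumococcal disease. It states none for the serotype contrast.

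The Background reports that, after PCV, "overall pneumococcal carriage prevalence is only slightly decreased (or unchanged) due to serotype replacement". The same paragraph says that vaccine types tend to be more likely to cause disease than replacement types, and that PCV may also protect against some cross-reactive serotypes.

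On available data: "Urine samples from adult cases enrolled prospectively in the adult surveillance programme, will be tested at the NCCD bacteriology laboratory" with BinaxNOW, and additional urine goes for the two SSUAD panels (the 13 PCV13 serotypes and 11 further PPSV23 serotypes). The PCV status of household children is among the recorded risk factors.

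**The concern.** A control condition in a vaccine-effectiveness study should be unaffected by the exposure. Here the exposure is a vaccinated child in the home, and the substudy rests on child-to-adult transmission within the household. If that child carries and passes on less VT pneumococcus, replacement means the child may carry and pass on more NVT. NVT pneumonia in the adult is then not a neutral comparator. Adjustment for district and time since introduction deals with replacement at community level. It does not deal with a difference between vaccinated and unvaccinated households in the same district and period.

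This is the only case-control contrast that isolates vaccine-type disease. No urine data exist from before PCV13, so the serotype trend analyses have no unvaccinated reference period. A reader who sees a test-negative label and a VE figure will take 1 − OR as protection against VT pneumonia, when part of it could be a shift in the comparator. Patients who would make a test-negative comparison possible are already enrolled but are not used in this contrast.

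**Working it through.** The article gives no sample size, power or VE for the nested study, so there is no figure of its own to reproduce.

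**1. What the odds ratio estimates.** With NVT controls, OR = RR(VT)/RR(NVT), so apparent VE = 1 − (1 − true VE)/RR(NVT). The values of RR(NVT) below are assumptions; the article gives none.

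| True VE | RR(NVT) | Apparent VE |
|---|---|---|
| 30% | 0.90 | 1 − 0.70/0.90 = 22% |
| 30% | 1.00 | 30% |
| 30% | 1.10 | 1 − 0.70/1.10 = 36% |
| 30% | 1.20 | 1 − 0.70/1.20 = 42% |

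**2. Are rises of 10% and 20% conceivable?** The Discussion cites, for adult CAP in the UK, 12.2% due to the additional PCV13 serotypes and 15.1% due to the additional PPSV23 serotypes. If these stand in for VT and NVT shares in unexposed households, case-for-case replacement of a 30% VT loss would raise NVT by 0.30 × 12.2/15.1 = 24%. The 10% and 20% scenarios then correspond to about 41% (10/24.2) and 83% (20/24.2) of full replacement. If replacement occurs only where VT disease is removed, a true VE of zero still appears as zero: replacement enlarges an effect but does not create one.

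**3. Precision.** SE(log OR) = √(sum of 1/cell count). From the article: 3500 prospective cases. Assumed: 60% with a chest radiograph consistent with CAP, 30% to 50% of these in households with eligible children (630 to 1050 adults), 80% of controls exposed, OR 0.7 (so 73.7% of cases exposed), and 3% pneumococcal but untyped. Two prevalence settings:

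- Low: VT 4.6% (the US figure in the Discussion), NVT 4% (assumed).
- High: VT 12.2%, NVT 15.1% (the UK figures in the Discussion).

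| Setting | VT cases | NVT controls | Negative controls | SE, NVT controls | SE, negative controls | Fall |
|---|---|---|---|---|---|---|
| Low | 29–48 | 25–42 | 557–928 | 0.65–0.51 | 0.44–0.34 | about 33% |
| High | 77–128 | 95–159 | 439–732 | 0.36–0.28 | 0.28–0.22 | about 22% |

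The gain is between one fifth and one third, smaller when pneumococcal positives are common.

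**4. What NVT versus negatives can show.** Its odds ratio estimates RR(NVT)/RR(negative), the household-level replacement that the VT-versus-NVT contrast assumes away. With 95 NVT cases, 439 negatives and 80% exposed in both, SE = √(1/76 + 1/19 + 1/351 + 1/88) ≈ 0.28, so the 95% interval spans a factor of exp(1.96 × 0.28) ≈ 1.7 either way. It can reveal a large shift but cannot exclude a 20% one, and should be reported as an estimate with its interval.

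**The case against.** The Background passage concerns carriage. Bias needs more adult NVT pneumonia in households with a vaccinated child than in unvaccinated households of the same district and period, and the article nowhere says it expects that. Its remark that replacement types cause less disease limits the size of any bias, and cross-reactive protection would reverse its sign. A reader might infer that VE is overstated, or that the contrast is invalid. The documents support neither: the direction is likely rather than established, the size is assumed, and VT versus NVT is a recognised design. NVT controls also share pneumococcal acquisition and urine detection with the cases, which is an advantage.

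Pneumococcal-negative controls have faults of their own. They include VT cases that the assays missed. The Background also cites falls in RSV- and influenza-associated pneumonia in children after PCV, so non-pneumococcal pneumonia may respond to the exposure too. Both pull the estimate toward no effect. A reader might infer that the two analyses bracket the truth, but they need not: if the exposure lowered both NVT and negative pneumonia by 10%, both contrasts would show 22% for a true 30%.

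Pneumococcal-negative patients are not lost to the substudy, since the radiological and hypoxia contrasts can include them, and changes in NVT serotypes over time are tracked separately. The separate analysis plan, which is not shown, may add control groups.

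All of this stands. It argues against making VT versus NVT secondary. It does not remove the mismatch between label, estimand and control group in the published text, or the case for a second control group.

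**Conclusion.** The point holds in limited form. The article fixes NVT pneumococcal pneumonia as the sole comparator in its one serotype-specific contrast, describes the design as test-negative, and reads the result as indirect VE without stating that household PCV13 must leave adult NVT pneumonia unchanged. Given the replacement in carriage that the Background describes, VE may be overstated, and that is the likelier direction.

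The illustrations (36% or 42% for a true 30%, or 22% in the opposite direction) rest wholly on assumed changes in NVT pneumonia and are not predictions. The precision gain of about one fifth to one third rests on the assumed radiograph, household, exposure and serotype fractions; the cited UK and US shares are stand-ins, as Mongolian adult serotype data do not yet exist. This is an inexpensive improvement to a secondary analysis, not a defect that invalidates it.

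**What to change.** 1. Keep VT versus NVT, name it an indirect-cohort comparison, and state beside it that 1 − OR equals indirect VE only if a vaccinated household child does not alter adult NVT pneumonia.
2. Prespecify a second control group: adults in eligible households with a chest radiograph consistent with CAP who are negative on BinaxNOW and on both SSUAD panels. Reserve the test-negative label for comparisons with this group.
3. Report VT versus negatives and NVT versus negatives, the latter as the check on household-level replacement, with intervals. State that missed VT cases and any PCV effect on viral pneumonia would pull the VT estimate toward no effect.
4. Use the same wording for cases and controls in the secondary objectives, Nested case-control study and Statistical analysis plan, restoring pneumococcal where it was dropped.

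The cost is protocol and analysis-plan wording and two extra regressions on data already planned for collection. No new patients or tests are needed. If the separate analysis plan already contains this control group, only the labelling, the stated assumption and the aligned wording remain.
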